#### Registered data

Patient-, tumor- and treatment-related characteristics and possible recurrence of disease will be collected from the NCR at the end of the study. These characteristics are routinely gathered in the NCR for all Dutch cancer patients. The NCR is hosted by the Netherlands Comprehensive Cancer Organization (IKNL) who has specially trained registrars extracting data directly from the patients files in all hospitals in the Netherlands. Additional relevant data (e.g. data on diagnostics/imaging, breast cancer-related hospital visits) will be retrieved from EHRs.

#### Outcomes

A detailed overview of all used instruments is provided in Table 1. Below a summary of outcome categories. The primary outcome to assess the effectiveness of personalized surveillance (PSP) and aftercare plans (PAP) will be patients’ experienced level of cancer worry and patients’ overall self-rated quality of life (EQ-VAS-score). Secondary outcomes will be: (1) quality of life including patients’ daily functioning and symptoms, (2) cost-effectiveness, by comparing societal costs and effects (i.e. healthcare costs, work productivity), (3) perceived risk of recurrence, (4) satisfaction and experiences with care, (5) patients’ need for support for fear of cancer recurrence, (6) shared-decision-making and (7) coping strategy in adjusting to cancer. Sociodemographic factors will be assessed in the first questionnaire: marital status, education level, work status, health literacy, social network and social engagement. Clinical characteristics will also be collected, namely tumor and treatment characteristics and possible cancer recurrences, which will be obtained from the NCR. Additional relevant data from the EHR, concerning the use of prediction models and patient decision aids, performance of imaging (i.e. conclusion of imaging, breast density, reason for consults) and pathology (i.e. type of biopsies, cytology, histology), detected recurrences and reason of breast cancer-related hospital visits, will be retrieved. This data from the EHR will be used to estimate healthcare costs and effects and to evaluate use of PSP and PAP.

#### Sample size

The sample size was estimated using a user-written script for mITS designs in the Statistical Analysis System (SAS) software program. Since we have two primary parameters, we correct for multiple testing using a Bonferroni correction and therefore set the statistical significance level at alpha = 0.025 (two sided). The effects we wish to measure are a difference of 1.52 on the Cancer Worry Scale (CWS; range 6–24) and a difference of 4.8 on the EQ-VAS score (range 0–100), which is part of the EQ-5D. This decision is based on our aim to detect a small to moderate difference of 0.4 times the standard deviation [24], which was found to be around 3.8 for the CWS [26] and 12 for the EQ-VAS score [27] in previous studies. From a clinical point of view, a difference of 1.52 on the CWS is relevant for our purpose to estimate the effectiveness of personalized follow-up: even a small decrease in cancer worry can lead to improved quality of life [28]. A difference of 4.8 on the VAS score is considered to be clinically relevant as well. We expect a correlation between the first two measurements within one hospital of 80%, and we expect this correlation to drop to 50% when comparing the first with the last measurement. In addition, we assume an intraclass correlation coefficient of 0.15. Taken 25% loss-to-follow up into consideration, each hospital will have to include four patients per period of three weeks in order to detect a difference of 1.52 on the CWS and 4.8 on the VAS score with 84%. The total inclusion time per hospital is 26 periods (78 weeks, or approximately 18 months), which amounts to a number of 104 patients per hospital and a study population of *N* = 1,040.

### Statistical analyses

An overview of the demographic and clinical characteristics will be provided using descriptive statistics. Continuous data will be expressed as a mean with the standard deviation (SD), or the Interquartile range (IQR) where appropriate. Categorical data will be expressed as frequencies (%). All questionnaires will be analysed in accordance with their corresponding manual. Self-composed questions (i.e. perceived risk of recurrence, adjusted questions from the CQ-Breast Index, demographics) will be analysed per item.

To assess the effectiveness of personalized surveillance and aftercare, all outcome parameters will be compared between the current-care and personalized-care groups. We will visualize the time series patterns pre- and post-personalization to assess a possible change in pattern after implementation of the personalization, for each hospital separately and combined. In this way we can also identify any underlying trends, seasonal patterns and outliers.

To test the change in level and slope associated with the personalization and to control for other (confounding and overall trend) effects, we will use segmented regression analyses in which piecewise regression lines will be fitted to each segment of time series, allowing each segment to exhibit different trends [29]. To correct for correlation between repeated measurements we will visually examine residual plots against time, which can additionally be statistically tested using the Durbin-Watson statistic. Autocorrelation will consequently be adjusted for by including the autocorrelation parameter in the segmented regression model [30]. Intention-to-treat analyses are done to estimate the effectiveness of personalized follow-up on the outcomes of the questionnaires. We will use the Bonferroni-Holm correction to adjust for multiple testing, meaning that the smallest two-sided p-value will be compared to 0.025 and if successful, the largest two-sided p-value will be compared to 0.05.

In case of missing data, we will record the percentage of drop-out and missing at each follow-up timepoint. If necessary, we will perform multiple imputation (if the assumptions for this technique are met) in order to ensure accurate analysis. In case some participants do not answer a section of the questionnaires, we will perform sensitivity analyses with and without the group with incomplete answers to detect possible differences in effects. Thereafter, we will perform meta-analyses to evaluate the combined results of all included hospitals. While the interrupted time series is generally considered the methodologically strongest non-randomized design, we will increase validity of its conclusions by confounder adjustment. As the effects are based on within-hospital comparisons, confounders at hospital level are dealt with by design. We will adjust for possible prognostic characteristics at patient level, i.e. patient-, tumour- and treatment-related characteristics (e.g., age, socioeconomic status, tumour and nodal stage, differentiation grade, receptor status, radiotherapy, systemic therapy, targeted therapy). Analyses to investigate effect modification and effect moderation by patient-, tumour- and treatment-related characteristics will be performed as well.

### Cost-effectiveness analysis

A cost-effectiveness and cost-utility analysis will be performed comparing costs and effects of “personalized follow-up care” versus “care as usual”, using a two-year (study-based; based on data from the current study) and lifetime (model-based; based on the study and extrapolations by means of data from literature) time horizon. We will derive information of the impact on personalized follow-up care on cancer worries, QoL, healthcare costs and (shift in) resources. 

Direct healthcare costs based on activities extracted from the EHRs (e.g. number of mammograms, consultations) will be multiplied by costs described in 'Benchmark costs from the Netherlands' or from the ‘Nederlandse Zorgautoriteit’ (NZa) [31]. For the costs of the interventions (decision support tools), an activity-based costing method will be performed for development, use and maintenance of the decision support platforms [32]. Indirect costs that will be taken into consideration are healthcare consumption outside the hospital and health-related productivity losses. Productivity losses will be measured by means of a selection of iMTA Productivity Cost Questionnaire (iPCQ) [33] and calculated by means of the Friction cost method, according to the International Society of Pharmaco-economical Organization and Research (ISPOR) guidelines [34].

The cost-effectiveness will be expressed in incremental costs per patient with a clinically relevant improvement on the CWS as primary outcome of the NABOR study. The cost-utility will be expressed in incremental costs per quality adjusted life years (QALYs) gained, obtained from the EQ-5D-5L (including the VAS) [27]. Long term consequences (after the timelines of this study), e.g. in terms of cancer worries and utilities, will be based on both the study results and literature to extrapolate the patient outcomes for a lifelong time horizon. The cost-effectiveness analysis will be performed by means of a state-of-the-art decision model, according to the guidelines for economic evaluations of the Dutch Zorginstituut (ZIN, [31]), like conducted by De Ligt and colleagues [35]. Uncertainty around the results will be quantified by means of non-parametric bootstrapping and cost-effectiveness acceptability curves, showing the possibility of the personalized follow-up care being whether or not cost-effective for various values of the Dutch society willingness to pay for one QALY [30].

## Discussion

This study supports the implementation of personalized surveillance and aftercare by developing and updating supporting tools and may provide new insights on the (cost-)effectiveness of personalized follow-up care, based on individual risks and needs.

### Risks and challenges

However, we foresee some risks and challenges that need a strategy. The first risk to encounter would be insufficient numbers of inclusion, which we will try to prevent by clear instructions, real-time monitoring of progress in each hospital and early assessment of barriers and facilitators. In the worst case a hospital turns out to be unable to achieve the required numbers of inclusion, we may approach other hospitals that expressed to be interested in participation. Second, structurally assessing patients needs before making decisions on personalized aftercare may identify more needs that were otherwise unknown, potentially resulting in more use of help and support. Although this may result in increasing costs at first, earlier treatment of symptoms may also prevent health effects later on. Next, it may be challenging to make shared decisions on the intensity of aftercare consultations within the limited capacity of the health care system. Therefore, management of patients’ expectations by communicating aftercare options and providing a clear explanation on what signals call for contacting a care provider is important. Another challenge is learned from the SHOUT-BC study, which already implemented the ‘Breast Cancer Surveillance Decision Aid’ and observed that care providers often not structurally explain available options and choices in surveillance and limitedly address patients’ considerations. Since the effectiveness of personalized surveillance depends on whether patients are well informed and involved in shared decision-making, we will provide early and intensive training of care providers, as well as evaluate the decision-making process post-implementation. Furthermore, it is known that patients and HCPs may be reluctant to opt for less intense surveillance, for instance because of patients’ fear of recurrence [12, 19, 36] or HCPs’ hesitance to rely on the risk information of the INFLUENCE nomogram. To promote use of risk information and open discussion of all surveillance options, the existing base of evidence [6, 7, 37, 38] regarding less intense surveillance schemes and use of risk information will be communicated before and during the transition period. At the end of the study, we can evaluate the eligibility of concerns regarding less intensive surveillance, since we also compare data on detected recurrences during patients’ participation with their individual risks, surveillance schemes and compare differences between patients who received CAU or a PSP. By collecting information on aftercare and surveillance consultations from the EHR, we can also evaluate whether a PAP and PSP is created and to what extent the actual provided care is in alignment with the decisions in the PSP and PAP. Lastly, the effectiveness of using a PSP and PAP may differ per patient and per hospital. Patients may benefit from the PSP and PAP differently, probably dependent on their tumour- and treatment-related characteristics, but also personal characteristics like their capability to understand and use the tools and ability to recognise and apply needs in decision-making. Also hospitals may differ because of differences in patient population, in involvement of care providers and in regional care networks. Therefore, our analyses will be based on within-hospital comparisons and adjusted for possible prognostic factors at patient level. Also, the heterogeneity between hospitals can contribute to complementary outcomes that are generalisable to daily clinical practice.

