## Methods

### Design

We use a prospective multicenter multiple Interrupted Time Series design (mITS) to compare the effectiveness of personalized follow-up (surveillance and aftercare) with current follow-up, taken the possible impact of changes over time into account. Through a continuous sequence of observations (i.e. data from questionnaires and registries), taken repeatedly at equal time intervals, underlying trends can be established on outcomes of interest. First, hospitals provide CAU for at least 12 periods of 3 weeks (approximately nine months) while including participants for this study (Fig. 1). Next, they enter stepwise the transition period of 9 periods of 3 weeks (approximately six months) in which HCPs receive training on using personalized surveillance (PSP) and aftercare plans (PAP) and supporting tools. From the transition period onwards, hospitals provide personalized care for all their patients who start with their follow-up (Fig. 1). During the transition period, no patients will be included in this study, since not all of them would be provided with both a PSP and PAP. After the transition period, hospitals will include participants for this study during the following 12 periods in which all patients will be provided with personalized care. It will take about nine months until all participating hospitals have entered the transition period and provide personalized care, which they will continue to provide after the end of inclusion of this study.

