### Treatment of subjects

#### Care as usual (CAU)

This study compares the effectiveness of personalized care to CAU, which is generally non-personalized. During the phase of CAU, all patients receive the usual type of follow-up care. For the majority of hospitals this includes annual mammography and physical examination combined with discussion of the results of the mammogram and aftercare consultations.

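### Evidence meant to change surveillance decisions is to be communicated before the transition period, when the same hospitals still enrol care-as-usual controls, so the baseline segment is at risk of contamination

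*Protocol article*

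**What the plan says.** The Design section separates the phases. It begins: "First, hospitals provide CAU for at least 12 periods of 3 weeks (approximately nine months) while including participants for this study". A transition of 9 three-week periods follows, "in which HCPs receive training on using personalized surveillance (PSP) and aftercare plans (PAP) and supporting tools". Enrolment stops for that time: "During the transition period, no patients will be included in this study". The reason given is that not every patient would yet receive both plans. Hospitals enter transition stepwise. The CAU section describes the comparator: "During the phase of CAU, all patients receive the usual type of follow-up care".

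The Risks and challenges section then takes up resistance to change: "it is known that patients and HCPs may be reluctant to opt for less intense surveillance". The remedy has a stated purpose, "To promote use of risk information and open discussion of all surveillance options", and a stated timing: the existing evidence "regarding less intense surveillance schemes and use of risk information will be communicated before and during the transition period". The same section also says that "we will provide early and intensive training of care providers".

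Statistical analyses specifies segmented regression for the change in level and slope, and describes the effects as within-hospital comparisons.

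**The concern.** What the early communication promotes is close to what the trial tests. The Introduction defines personalized surveillance by individual risk estimates, preferences and shared decisions. Study setting selected hospitals that did not yet personalize follow-up and gives risk-based surveillance as an example. Promoting risk-based discussion before transition encourages, during the control phase, a practice that site selection required to be absent.

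The Design section stops inclusion during transition because of partial exposure, so the hazard was recognised there. No corresponding protection is stated for the end of the CAU phase.

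At stake is the baseline. Each hospital is its own control. The statement that hospital-level confounders are handled by design does not cover a change in practice within a hospital during its CAU phase. Segmented regression projects the CAU line across a 9-period gap, so even a modest disturbance of that line can move the estimated level change. Shared decision-making, measured only at T1, and the mammogram and consultation counts used in the cost comparison are exposed to the same risk.

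**Working it through.** **Timeline.** Before transition: CAU care with inclusion open (Design), and evidence communication under way (Risks and challenges). During transition: training and communication, inclusion closed. After transition: personalized care, inclusion open. The overlap lies in the first phase, unless all communication came before CAU inclusion began. In that case the whole baseline could be shifted.

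**The plan's figures (Sample size, Design).** Target effect: 0.4 × 3.8 = 1.52. Inclusion: 26 periods × 4 patients = 104 per hospital, and × 10 = 1,040. With 12 post-transition periods, 26 − 12 = 14 CAU periods, which agrees with the stated minimum of 12. The 84% power comes from a script that is not shown. It cannot be reproduced, and this point does not depend on it.

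**Model.** Ordinary least squares, separate trends before and after, a 9-period gap, 12 post periods, and a true reduction of 1.52 in every post period. A leak of 25% is 0.25 × 1.52 = 0.38 points in each affected CAU period. Leak size and placement are both assumptions; the documents give neither. Reductions are written as negative values.

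For n CAU periods, the fitted CAU line has mean ȳ and slope b = Σ(t − t̄)y / Sxx, with t̄ = (n + 1)/2 and Sxx = n(n² − 1)/12. The first post period is s = n + 10. The baseline projected to that period is ȳ + b(s − t̄). The estimated level change is −1.52 minus that projection.

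1. *Last 3 of 12 periods.* t̄ = 6.5, Sxx = 143, s = 22. ȳ = −0.38 × 3/12 = −0.095. b = −0.38 × (3.5 + 4.5 + 5.5)/143 = −0.0359. Projection: −0.095 − 0.0359 × 15.5 = −0.651. Level change: 1.52 − 0.651 = **0.87**.
2. *Last 3 of 14 periods.* t̄ = 7.5, Sxx = 227.5, s = 24. ȳ = −0.0814. b = −0.38 × (4.5 + 5.5 + 6.5)/227.5 = −0.0276. Projection: −0.536. Level change: **0.98**.
3. *Flat over all CAU periods.* b = 0, projection −0.38. Level change: 1.52 − 0.38 = **1.14**, whatever the number of periods.
4. *First 3 of 12 periods, then none.* ȳ = −0.095, b = +0.0359. Projection: −0.095 + 0.556 = +0.461. Level change: 1.52 + 0.461 = **1.98**.

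**Sensitivity.** A 10% leak in the last 3 of 12 periods gives 1.26. A 25% leak in the last 6 of 12 gives 0.59. With a common slope, case 1 gives 1.05. A plain difference in means in case 1 gives 1.52 − 0.095 = 1.425, so most of the loss in case 1 comes from projecting the tilted line. With longer CAU series the late leak matters less: 1.13 with 18 periods and 1.25 with 24.

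**The case against.** The documents do not say that CAU practice will change. The CAU section says the opposite, and personalized care starts only from transition. A reader might infer that the comparator is contaminated and its trend tilted toward the intervention. The text supports only a risk. No recipient is named: care providers are strongly implied by the reference to their hesitance, and patients may be meant too. The timing could be site set-up, since Study setting describes visits to the candidate hospitals. The promise of early training does not show exposure during CAU, because the Design section places training in transition.

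A reader might also infer that any leak is amplified into an under-estimate. That does not follow. Amplification needs a late leak. A flat leak reduces the effect one for one, and an early leak that fades inflates it. The figure of 0.87 also uses the minimum CAU length.

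A 25% leak may be generous. The communication concerns surveillance and not aftercare, and it comes without the trained use of the tools. The protocol itself reports that in the preceding study providers often did not explain the options systematically even with the decision aid in place.

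The planned health-record data on imaging, visits and use of prediction models, and the plots per hospital, could reveal drift, though neither is described as a safeguard.

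All of this stands against certainty and against any single figure. It does not remove the conflict between the stated timing and the separation of phases.

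**Conclusion.** The point holds as a design risk. The protocol schedules communication intended to alter surveillance discussions in a phase that its own design reserves for unaltered care, and the article states no protection for that phase. In the scenarios with a 25% leak in 3 periods or throughout CAU, an effect of 1.52 would be estimated at anything from 0.87 to 1.98. Direction and size depend on when the communication happens and how much practice moves, and the documents fix neither. A late or sustained leak biases toward no effect; an early, fading one biases away from it. The correction is worth making because it is cheap and the baseline carries the whole comparison.

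**What to change.** In Risks and challenges, delete the reference to the time before transition, so that the communication of this evidence to care providers and patients takes place during the transition period only. State that this applies hospital by hospital, because entry is stepwise and a study-wide message could reach later hospitals in mid-CAU. Leave the needs assessment, co-creation and usability work described under the Personalized Aftercare Plan in place. A ban on all contact about the tools would be too broad, since that work needs care providers.

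Recruitment is already under way. Where such communication has gone out:

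- record its date for each hospital;
- run a sensitivity analysis that drops that hospital's CAU periods after the date or, if it preceded CAU inclusion, state that the baseline may be shifted;
- use the planned health-record data on imaging, visits and use of prediction models to check for drift within CAU.

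The cost is one changed sentence and a dated log. Persuasion is concentrated in the existing transition of 9 × 3 = 27 weeks, and the sensitivity analysis loses some CAU periods and therefore precision.

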**Methods:**

A prospective multicenter multiple interrupted time series (MITs) design is being used. In this design, 10 participating hospitals will be observed for a period of eighteen months, while they -stepwise- will transit from care as usual to PSPs and PAPs. The PSP contains decisions on the surveillance trajectory based on individual risks and needs, assessed with the ‘Breast Cancer Surveillance Decision Aid’ including the INFLUENCE prediction tool. The PAP contains decisions on the aftercare trajectory based on individual needs and preferences and available care resources, which decision-making is supported by a patient decision aid. Patients are non-metastasized female primary breast cancer patients (*N* = 1040) who are curatively treated and start follow-up care. Patient reported outcomes will be measured at five points in time during two years of follow-up care (starting about one year after treatment and every six months thereafter). In addition, data on diagnostics and hospital visits from patients’ Electronical Health Records (EHR) will be gathered. Primary outcomes are patient-reported cancer worry (Cancer Worry Scale) and overall quality of life (as assessed with EQ-VAS score). Secondary outcomes include health care costs and resource use, health-related quality of life (as measured with EQ5D-5L/SF-12/EORTC-QLQ-C30), risk perception, shared decision-making, patient satisfaction, societal participation, and cost-effectiveness. Next, the uptake and appreciation of personalized plans and patients’ experiences of their decision-making process will be evaluated.

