## Introduction

Each year in the Netherlands, about 15.000 non-metastasized female breast cancer patients start with their follow-up [1]. This growing number of breast cancer survivors increases the demand on follow-up care, which consists of surveillance and aftercare. Surveillance focuses on early detection of locoregional recurrences (LRR) or second primary breast cancers (SPBC) using mammograms and physical examination. Aftercare focuses on prevention, early recognition and treatment of possible (late) physical or psychological effects of breast cancer and its treatment [2].

Currently, most Dutch hospitals organize surveillance as ‘one-size fits all’ [2], following the national guideline by offering an annual mammogram and physical examination. However, the benefits of these pre-scheduled surveillance visits are limited and may differ by patient. The risk of recurrence is low [3], depends on patient-, tumor- and treatment-related characteristics and varies over time [4–6]. For women with a low risk, annual mammograms may be too frequent. Especially since studies have shown that more surveillance does not guarantee less severe recurrences [7, 8] and about half of the recurrences are detected outside of scheduled visits by patients themselves [9]. Intense surveillance has not only limited benefits, but also places a burden on patients and healthcare. For patients, surveillance may provoke distress and cancer worry, which is a very prevalent concern among cancer survivors and can negatively impact quality of life [10]. Even more, it may contribute to unrealistically high expectations of the benefits of surveillance and risk perceptions, which hinder the patient’s transition to normal life [11]. Concerning healthcare, intense surveillance may lead to unnecessary costs and use of limited care resources, especially when provided even more intensively than guidelines recommend [7, 12]. Taken together, current organization of surveillance neglects patients’ prognoses and preferences, which may cause unnecessary burden and less efficient care.

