**Fig. 2 Fig2:**
[figure not shown]
Participant timeline. The procedure for patients included during CAU and personalized care are the same. Moment of first measurement is one year after treatment is ended, around the first mammogram. NCR = Netherlands Cancer Registry; EHR = Electronic Health Records. *only applies to a subsample of the first 50 patients included during care as usual (CAU) and the first 50 patients included during personalized care

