#### Questionnaires

An overview of all questionnaires and used instruments is provided in Table 1. A baseline questionnaire (T1) will be sent to patients, via e-mail or post, after informed consent is signed (i.e. approximately one year after initial treatment). Subsequently, patients will receive five follow-up questionnaires during two years: after six (T2), twelve (T3), eighteen (T4) and twenty-four (T5) months. For a subsample of patients (the first 50 patients included in the current care phase and the first 50 patients included from the personalized care phase) we will collect for an additional two years the health care consumption. This longer follow-up enables estimation of cost-effectiveness over a 5-year period, which is currently the standard duration of follow-up in hospitals. Therefore, this subsample receives four extra questionnaires: after thirty (T6), thirty-six (T7), forty-two (T8) and forty-eight (T9) months. The time it takes to complete the questionnaires differs per measurement moment. The T1 questionnaire takes about 45 min to complete, the T3 and T5 questionnaires take around 30 min and the T2 and T4 (and T6, T7, T8 and T9) questionnaires take around 15 min to complete.

**Table 1 Tab1:** Detailed overview of included measures in the patient questionnaires

Measure	Description	Scoring range	T1	T2	T3	T4	T5	T6	T7	T8	T9
Cancer worry; CWS [26] (primary outcome)	6-item, 4-point scale measures concerns about cancer recurrence and the impact of these concerns on daily functioning	Range 6–24, higher scores indicate greater worrying	X		X		X				
Self-rated quality of life; VAS score [27] (primary outcome)	1 item, measures patients’ health-related quality of life	Range 0–100, higher scores indicate greater health-related quality of life	X		X		X				
Quality of life (EQ-5D-5L) [27]	5 items, 5-point scale measures patients’ health-related quality of life		X		X		X				
Short-Form health index (SF-12) [39]	12 items with 2–6 response options on quality of life	Mental and physical component score based on the US population scoring system, higher scores indicate greater quality of life	X		X		X				
Physical symptoms scale of the EORTC-QLQ-C30 [40]	13 items, 4-point scale measure physical symptoms		X		X		X				

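### Recurrences detected over two years cannot settle concerns about less intensive surveillance, because detection depends on imaging and events are few

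*Protocol article*

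**What the plan says.** The Risks and challenges section notes that patients and care providers may hesitate to choose less intense surveillance. It answers that "we can evaluate the eligibility of concerns regarding less intensive surveillance, since we also compare data on detected recurrences". The material to be compared is "detected recurrences during patients’ participation with their individual risks, surveillance schemes and compare differences between patients who received CAU or a PSP".

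Other sections fix the setting:

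- **Window.** The abstract gives the length of participation: "Patient reported outcomes will be measured at five points in time during two years of follow-up care". The Questionnaires section extends follow-up only for the first 50 patients of each phase, and only for one purpose: "we will collect for an additional two years the health care consumption".
- **Start.** The legend to Fig. 2 says: "Moment of first measurement is one year after treatment is ended, around the first mammogram". This applies to both phases.
- **Imaging.** Care as usual (CAU) is annual mammography in most hospitals. The personalized surveillance plan (PSP) allows annual or less frequent mammography, chosen per patient.
- **Detection and risk.** According to the Introduction, "about half of the recurrences are detected outside of scheduled visits by patients themselves", and "The risk of recurrence is low [3], depends on patient-, tumor- and treatment-related characteristics and varies over time". No recurrence rate is given.
- **Sources.** The Registered data section says that "possible recurrence of disease will be collected from the NCR at the end of the study". The Outcomes section adds imaging conclusions, pathology, detected recurrences and reasons for visits from the health records. Size or stage of the recurrence is not named.

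**The concern.** Imaging frequency is both the exposure under question and a means of finding the outcome. If about half of recurrences surface outside scheduled visits, up to about half may depend on those visits. A patient imaged less often may carry a recurrence that is found only after the window closes. A lower count under personalized care would then fit two opposite situations: less imaging does no harm, or recurrences are being found later. The Introduction describes the purpose of surveillance as early detection and discusses the severity of recurrences. The number found in two years measures neither.

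The other two comparisons in the sentence do not repair this. Under-detection also pushes observed recurrences below predicted risk. Comparison by chosen scheme is confounded, because the scheme is meant to follow the individual risk.

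Results go to the national guideline working group, so an equal or favourable count could be given more weight than it can bear.

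**Working it through.** **1. Size of the comparison.** The plan's figure reproduces: 4 patients × 26 periods × 10 hospitals = 1,040. An equal split, assumed here, gives 520 per phase. The 84% power in the Sample size section concerns the Cancer Worry Scale and the EQ-VAS. No event number, margin or power is stated for recurrence.

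**2. Effect of imaging frequency on detection, equal true risk.** The documents give no natural history, so these inputs are assumptions:

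- recurrences become detectable at a constant rate;
- symptoms follow after an exponential time with mean s of 1, 1.5 or 2 years;
- mammogram sensitivity is 85%;
- every patient has a mammogram at T1.

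Write f(t) = exp(−t/s). Results are in units of the yearly rate, which cancels in the ratio. For s = 1.5, f(1) = 0.513 and f(2) = 0.264.

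*Window closing just before the month-24 mammogram*

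- Two-yearly imaging (no mammogram after T1 in the window): 0.15·s·(1 − f(2)) + 2 − s·(1 − f(2)) = 0.166 + 0.895 = 1.061.
- Annual imaging adds the recurrences found at month 12 that would otherwise surface after month 24. The detectable pool at month 12 is 0.15·s·f(1) + s·(1 − f(1)) = 0.845. The addition is 0.85 × 0.845 × 0.513 = 0.369, and the total is 1.430.
- Ratio: 1.061 / 1.430 = 0.74.

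*Window including the month-24 mammogram*

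- Annual: pool at month 24 is 0.15 × 0.845 × 0.513 + 0.730 = 0.795. Total: 1.430 + 0.85 × 0.795 = 2.106.
- Two-yearly: pool is 0.15 × 1.5 × 0.264 + 1.105 = 1.164. Total: 1.061 + 0.85 × 1.164 = 2.050.
- Ratio: 2.050 / 2.106 = 0.97.

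The same formulas for the other values of s agree with a simulation of this model:

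| Mean detectable phase | Month-24 mammogram outside, full uptake | Outside, 50% uptake | Inside, full uptake |
|---|---|---|---|
| 1 year | 0.85 | 0.92 | 0.98 |
| 1.5 years | 0.74 | 0.87 | 0.97 |
| 2 years | 0.65 | 0.82 | 0.96 |

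Uptake u enters as 1 − u + u × ratio. As a plausibility check, with the month-24 mammogram outside the window, the model's share of annual-group recurrences found by mammogram is 0.40, 0.50 and 0.58. That brackets the share implied by the Introduction.

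T1 lies around a mammogram and participation ends at month 24, so the decisive imaging round sits on the edge of the window. The text does not say on which side.

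**3. Precision with no bias at all.** Events per group = 520 × 2 × yearly risk, with the yearly risk assumed. The 95% interval of the rate ratio at equal counts e is exp(±1.96 × √(2/e)).

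| Yearly risk | Events per group | 95% interval |
|---|---|---|
| 0.5% | 5.2 | 0.30 to 3.37 |
| 1.0% | 10.4 | 0.42 to 2.36 |
| 1.5% | 15.6 | 0.50 to 2.02 |
| 2.0% | 20.8 | 0.54 to 1.84 |

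Power to detect a doubling (two-sided 0.05, two proportions) is Φ{(Δ − 1.96·√(2p̄(1 − p̄)/n)) / √((p₀q₀ + p₁q₁)/n)}. For 2% against 4% with n = 520 it is Φ{(0.02 − 0.0207)/0.01056} = 47%. For two-year risks of 1%, 3% and 4% it is 26%, 65% and 78%.

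**The case against.** **The deficit may be small.** A reader might infer that personalized surveillance is bound to look safe or safer, or that its detected number will be halved. The documents support neither. Annual imaging remains an option, uptake of less imaging has no figure, and the protocol itself expects reluctance. If the month-24 mammogram is inside the window, two-yearly imaging nearly catches up. A ratio near 0.5 needs patients with no mammogram through month 24, set against annual patients whose month-24 mammogram counts (1.061 / 2.106 = 0.50 in the model). With so few events, chance can also reverse the sign. All this stands. What remains is a tendency of known direction and uncertain size.

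**More than a count is planned.** The text speaks of comparing data on recurrences, and reasons for visits, imaging conclusions and pathology are collected. Mode of detection can be described from these. Comparison with individual risk and adjustment for prognostic factors are also planned, and they help against confounding. This stands too, but neither removes under-detection or narrows the interval.

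**No safety conclusion is announced.** Recurrence is not a listed primary or secondary outcome, and the claim is one Discussion sentence in a condensed article. A reader might infer that a low count will be presented to the guideline group as proof of safety. The documents say only that results will be shared. The hesitance described also includes doubt about the risk tool, on which observed against predicted recurrences does bear. This limits the weight of the point. It does not give the design the ability that the sentence asserts.

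**Conclusion.** The statement is wrong as written, in a limited sense: recurrences detected in two years cannot evaluate concerns about less intensive surveillance. There are two independent reasons.

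The first is bias. Detection depends partly on imaging frequency, so less imaging tends to lower the detected number when true risk is equal. The reduction is roughly 15% to 35% at full uptake of two-yearly imaging if the month-24 mammogram is outside the window, and 2% to 4% if it is inside. These sizes rest on the assumed natural history and sensitivity.

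The second is precision. At an assumed 0.5% to 1.5% per year, equal counts would still leave a doubling of the rate within the 95% interval. This reason holds even if the bias is nil.

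The primary outcomes and their analysis are unaffected. The point concerns what the trial may conclude about recurrence, and it should be corrected before results are reported.

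**What to change.** 1. Reword the sentence in Risks and challenges: two-year detected recurrence is descriptive and cannot support a conclusion that less imaging is safe.
2. Define one window, counted from T1, that contains the same imaging round in both phases. Extraction at the end of the study does not by itself fix a common time since T1.
3. Report mode of detection (scheduled imaging, or outside scheduled visits) from the health-record data already planned. Where registry or pathology data allow, add size or stage at detection.
4. Compare by phase (CAU against personalized care), adjusted for INFLUENCE risk and with a confidence interval, rather than by chosen scheme.

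A later registry linkage would inform on delayed detection. It is optional, extends the scope and is subject to consent.

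The cost is a weaker statement than the one now promised and a little more analysis. The data are largely collected already, and nothing here touches the surveillance options offered to patients.
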